### Participants

#### Aim 1: Incidence Cohort (n=100)

Children with SCD (n=50) under 9 months of age with all SCD genotypes and their caregivers will be recruited from the Sickle Cell Clinic at SLCH. Children without SCD (n=50) will be recruited as a comparison cohort and matched at the group level to the SCD cohort on the distributions of age, sex, race, socioeconomic status, and Area Deprivation Index [32], rather than paired individually. Group-level matching will be finalized after enrollment. Typically developing children will be recruited through SLCH general medicine, community early childhood centers, local pediatricians, public libraries, local early intervention providers, and faith-based organizations, using methods previously successful in this lab [33,34]. Children will be excluded if they have a diagnosis associated with developmental delay that is not attributable to SCD, or if the family is not English-speaking.

Caregivers of children with SCD will be approached by phone or following a regularly scheduled clinic visit. Interested caregivers will review the informed consent document with a member of the research team by phone, Health Insurance Portability and Accountability Act (HIPAA)–secure video call, or in person.

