#### Aim 2: Intervention Cohort (n=25)

An additional 25 infants with SCD under 9 months of age will be recruited for the SCCCD intervention following the same inclusion and exclusion criteria as aim 1. Following the 9-month baseline evaluation, consenting families will participate in the 12-month SCCCD program.

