The Ages and Stages Questionnaire, Third Edition (ASQ-3) is a caregiver report screener used widely in primary care and research settings that assesses development across the domains of communication, gross motor, fine motor, problem solving, and personal-social skills in approximately 10 minutes [10,40]. While the ASQ-3 is time- and cost-efficient, it is insufficiently detailed to identify early indicators of mild-to-moderate developmental delays when used alone [5,10,18,20,41,42].

The Survey of Well-Being of Young Children (SWYC) is a brief, validated caregiver report screener that captures developmental and behavioral milestones as well as family context factors including caregiver depression and social determinants of health [43,44]. The SWYC was added to the protocol following community partner and community advisory board input to capture additional environmental and contextual factors and to allow comparison with other commonly used screening measures.

The Infant Toddler Activity Card Sort (ITACS) is a picture-based caregiver report tool developed and validated by members of this team to identify concerns related to child participation in family activities and routines [33,34,45]. Caregivers are presented with photographs depicting common infant and toddler activities and asked to identify those that present a challenge for their child.

The Behavior Rating Inventory of Executive Function-Preschool (BRIEF-P) is a widely used caregiver report measure of executive functioning for children as young as 2 years of age, designed to identify how a child functions within the context of their individual environments [46]. The BRIEF-P will be administered at the 30-month time point only.

The Infant Toddler Home Observation for Measurement of the Environment Inventory [9] is a 42-item checklist completed by a research team member that evaluates the quality and quantity of stimulation and support available to the child in the home environment [47]. The HOME (Infant Toddler Home Observation for Measurement of the Environment) will be administered at all 3 time points for children enrolled in aim 2.

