The Patient-Reported Outcomes Measurement Information System (PROMIS) Depression Short Form (8 items) will be completed by caregivers at each time point to assess caregiver mental health, given the established association between caregiver depression and child developmental outcomes [16,48,49]. Caregivers with concerning scores on the PROMIS Depression screener, based on prespecified cutoffs, will be referred to behavioral health services.

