### Data Analysis

#### Aim 1

Evaluations will be scored according to their respective manuals. Mixed effects regression will be used to analyze developmental outcome data, with time, group, and time-by-group interaction entered as fixed effects. This approach accounts for within-subject and within-group variability across the 3 longitudinal time points. Scores from the Bayley-4 will be compared to the ASQ-3. Covariates will include race, age, sex, caregiver education, socioeconomic status, disease-modifying medication use, and therapeutic intervention received. The number of evaluations completed and any therapeutic or behavioral interventions received (eg, physical therapy, OT, speech-language therapy) will be documented. Children who receive therapy services during the study period will be analyzed separately.

#### Aim 2

Standardized scores will be calculated for each assessment according to the respective manuals. Scores greater than 1 SD below the mean will be classified as a developmental delay. Repeated measures ANOVA will be used to compare group mean scores at 9, 18, and 30 months. Logistic regression will compare the number of children classified with a delay at 30 months to the aim 1 cohort. The number of caregivers approached and enrolled will be documented, and visits scheduled and completed, along with topics from visit notes, will be summarized. Additional analyses will examine possible changes in the home environment and caregiver mental health before and after the intervention. When the outcome is binary, a mixed effects logistic regression will be used, with time, group, and time-by-group interaction entered as fixed effects and variation of subject intercept as a random effect. Time will also be tested as a random effect in a more elaborate model.

#### Aim 3

Two research team members will use an iterative inductive and deductive thematic analysis approach to review all transcripts and generate themes for a preliminary codebook [60]. The preliminary codes will be applied to 4 interviews using NVivo software; any deviations will be discussed, and the revised codebook will be applied to all remaining interviews [62]. Codes will be analyzed for themes, and participation data from aim 2 will be summarized and integrated with qualitative findings [63,64].

The study protocol and deidentified data will be made available from the corresponding author on request and consistent with the NIH Data Management and Sharing Plan.

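### Aim 2 examines change in caregiver depression without a comparator, although Aim 1 caregivers of children with SCD complete the same form at the same visits

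*Protocol article*

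**What the plan says.** In the protocol article, Data Analysis, Aim 2, the planned contrast for the two family outcomes is: "Additional analyses will examine possible changes in the home environment and caregiver mental health before and after the intervention". No comparison group is named there.

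The Measures section says that the PROMIS Depression short form "will be completed by caregivers at each time point to assess caregiver mental health". Table 1 lists it at 9, 18 and 30 months for Aims 1 and 2. The same section adds: "Caregivers with concerning scores on the PROMIS Depression screener, based on prespecified cutoffs, will be referred to behavioral health services". Neither that sentence nor its counterpart under Ethical Considerations limits the referral to one aim. The HOME Inventory, by contrast, "will be administered at all 3 time points for children enrolled in aim 2", and Table 1 lists it for Aim 2 only.

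On the cohorts, the plan says of Aim 2: "An additional 25 infants with SCD under 9 months of age will be recruited for the SCCCD intervention". Of Aim 1 it says: "Children with SCD (n=50) under 9 months of age with all SCD genotypes and their caregivers will be recruited". Eligibility is shared between the two SCD cohorts, because Aim 2 enrols families "following the same inclusion and exclusion criteria as aim 1".

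**The concern.** A before-after change in one treated group adds any effect of SCCCD to everything else that happens over the same period. Two such influences can be read from the plan itself. One is the passage from infancy to toddlerhood. The other is referral of caregivers with concerning depression scores, which can move the measured outcome whether or not a family receives SCCCD.

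The Introduction presents caregiver stress and the home environment as part of the reasoning behind the intervention, and Aim 2 is meant to inform a randomised trial. A fall in PROMIS scores could therefore be taken as support for that reasoning when the analysis cannot tell the sources apart. The reverse can also happen: if caregiver mood worsens with time, a real benefit could be hidden.

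**Working it through.** **Which visits carry the contrast.** Under Procedures, SCCCD starts after the 9-month evaluation and lasts 12 months, with up to 15 to 18 months allowed.
- Delivery ends at about 9 + 12 = 21 months of age, and at the latest about 9 + 18 = 27 months.
- The 18-month visit falls during delivery, so 30 months is the only visit after it.
- Before versus after therefore spans about 30 − 9 = 21 months.

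**Does another sentence supply the comparator?**
- The logistic regression in Data Analysis, Aim 2, compares delay at 30 months with the Aim 1 cohort. That is a developmental outcome.
- The model with time, group and time-by-group terms is stated for binary outcomes. No section says that PROMIS will be dichotomised for analysis.
- The repeated measures ANOVA compares group means but does not name the groups.
- Limitations describes the comparison with Aim 1, and its selection-bias caveat, for developmental outcomes.

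None of these covers the PROMIS score or HOME.

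**Is a comparator scheduled?** For PROMIS, yes: same form, visits, eligibility criteria and referral rule, with 50 Aim 1 SCD families planned. For HOME, no.

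**Illustration of size.** The article gives no PROMIS SD, correlation, time trend, alpha or power for this analysis, so there is no stated figure to reproduce. All of the following are assumptions: SD 10, correlation r = 0.6 between 9 and 30 months (range 0.5 to 0.7), two-sided 5% test, all planned families observed.

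SD of change = 10 × √(2(1 − r)) = 10 × √0.8 = 8.94.

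Before-after SE = 8.94 / √25 = 1.79.

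Difference-in-change SE = 8.94 × √(1/25 + 1/50) = 8.94 × 0.245 = 2.19.

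Probability that a paired t test (noncentral t, 24 df) is significant when SCCCD has no effect:

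| Assumed background change | r = 0.5 | r = 0.6 | r = 0.7 |
|---|---|---|---|
| 0 points | 5% | 5% | 5% |
| 2 points | 16% | 19% | 24% |
| 3 points | 30% | 36% | 46% |
| 4 points | 48% | 57% | 70% |

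If both cohorts share the background change, it cancels in the difference and the rate returns to 5%. The price is precision: at r = 0.6 the difference detectable with 80% power is (1.96 + 0.84) × 2.19 = 6.1 points, against 5.0 for the before-after change.

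**How much comparator data there will be.** Table 4 shows 9-month evaluations for 12 of the 26 Aim 1 SCD participants so far, and 24 more are to be recruited. If participants without a recorded 9-month evaluation have passed that age, at most 12 + 24 = 36 can supply an observed 9-to-30-month change. With 36, the SE is 8.94 × √(1/25 + 1/36) = 2.33. With 12 alone it would be 8.94 × √(1/25 + 1/12) = 3.14. A mixed model also uses the 18- and 30-month scores of the others, which recovers part of the loss.

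**The case against.** A reader might infer that the plan will credit natural change to SCCCD. The text does not say so. It speaks of possible changes, in additional analyses, within what Study Design and Setting calls a feasibility pilot, and no section attributes a PROMIS or HOME change to the intervention. That objection stands.

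It can also be said that the missing comparator is inferred from silence in a condensed article. PROMIS classified by its cutoffs could enter the binary model, and details of secondary analyses often sit in an analysis plan. This has some force. But the article does state a contrast for caregiver mental health, and that contrast is before versus after. Where a comparison with Aim 1 is intended, the article says so.

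Regression to the mean is a tempting further argument but has little force: nobody is selected on PROMIS, so the cohort mean need not drift for that reason. Referral reaches only caregivers with concerning scores, so its effect on the mean of 25 is diluted.

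The proposed comparator has weaknesses too. It is not randomised. It is also partly earlier: at May 31, 2026, Table 4 shows 18 Aim 1 SCD evaluations at 30 months, while Aim 2 had only its five 9-month evaluations. The cohort comparison reduces the bias from shared change but does not remove selection or calendar-time differences.

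**Conclusion.** The point holds as a minor one on a secondary analysis. As written, the PROMIS contrast cannot separate SCCCD from change with child age or from behavioral-health referral, and a less biased contrast is already scheduled.

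The rejection rates in the table must not be read as this study's false-positive rates. They illustrate what follows from an assumed SD, correlation and background change, none of which the article gives; even the direction of any background change is unknown. The statement that shared change cancels depends on the two SCD cohorts having the same background course.

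For HOME there is no internal reference, so the point is only how the result is labelled. The Bayley-4 primary outcome is not affected.

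**What to change.** In Data Analysis, Aim 2:

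1. State that the PROMIS Depression score will be analysed with a mixed model with time, cohort and time-by-cohort as fixed effects, comparing Aim 2 with Aim 1 SCD caregivers on all available visits, and that the cohort difference in change from 9 to 30 months is the quantity of interest.
2. Report the change within Aim 2 as descriptive.
3. Report the HOME change as descriptive and not as evidence of an SCCCD effect.

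In Limitations, extend the selection-bias caveat to the PROMIS comparison, and note that part of the Aim 1 cohort was assessed earlier and that few of its members so far have a 9-month evaluation.

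This adds no visits or measures. It costs a wider interval, about 2.2 against 1.8 points in SE under the assumptions above and somewhat more if 9-month scores remain sparse. It also brings reliance on a non-randomised comparator and a weaker statement about HOME.

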### Missing Data and Attrition

Participants who do not complete all evaluation time points will be analyzed using available data. Attrition will be documented across all aims, including the number of participants who withdraw, are lost to follow-up, or miss individual evaluation visits, and patterns of missingness will be reported.

### Ethical Considerations

This study has been approved by the Human Research Protection Office at Washington University School of Medicine (IRB 202104034 and 202407080), approved April 2021 and July 2024, respectively. This study poses minimal risks to children and families. Study personnel will complete mandated reporter training, and caregivers will be referred to supportive services if any psychological, environmental, or developmental concerns arise. All study procedures will be conducted in accordance with the ethical standards of the IRB.

Informed consent will be obtained from the parent or legal guardian for themselves and on behalf of the child before any study procedures. The consent process will take place in a private setting and will be conducted in person, by phone, or via HIPAA-secure video call. Caregivers will be given time to ask questions and will receive a copy of the signed consent document. Since all child participants are under 3 years of age, child assent will not be obtained. Caregivers may withdraw from the study at any time without consequence.

All data will be stored with 2 levels of password protection. Paper consent documents will be maintained in a locked cabinet in a locked office on the Washington University School of Medicine campus. Digital data will be collected via REDCap and will be accessible only to members of the research team. Any identifying information will be coded so that it can only be linked to individual participants by the research team.

The risks associated with this study are no greater than those encountered during a routine clinical or therapy visit. Caregivers may experience mild stress or anxiety when discussing their child’s development. To mitigate this, all research team members will be trained in strategies for communicating sensitively about developmental concerns with caregivers. All research staff interacting with participants will also complete mandatory reporter training for child abuse and neglect. Caregivers will have the option to complete surveys verbally if preferred. Caregivers with concerning scores on the PROMIS Depression screener will be referred to behavioral health services.

## Results

A total of 128 caregivers have been approached, and 72 have consented. Of those, 13 participants withdrew because of time constraints, interest, or loss to follow-up. As of May 31, 2026, a total of 26 unique participants with SCD have participated in aim 1, and 24 unique participants participated in the comparison cohort. For aim 2 with the pilot intervention, 13 caregivers have been approached and 7 have consented, and 5 caregiver or child dyads have been enrolled and have participated. Two caregivers withdrew due to moving out of state or living outside of the intervention radius (>60 miles). Characteristics of participants to date are available in Tables 2 and 3. Enrollment data can be seen in Table 4.

**Table 2. T2:** Caregiver demographics.

Demographics	Sickle cell cohort (aim 1; n=26)	Typically developing cohort (aim 1; n=24)	Sickle cell cohort (aim 2; n=5)
Parental role			
Mother, n	23	22	5
Father, n	3	2	0
Age (y), mean (SD)	30.9 (7.4)	33.4 (5.0)	28.8 (7.9)
Age group (y), n			
20‐29	17	6	2
30‐39	5	15	3
40‐49	4	3	0

**Table 3. T3:** Child demographics.

Demographics	Sickle cell cohort (aim 1), n	Typically developing cohort^a^ (aim 1), n	Sickle cell cohort (aim 2), n
Gender			
Male	13	13	3
Female	13	11	2
Race or ethnicity			
White	0	15	0
Black or African American	25	7	5
Asian	0	1	0
More than one race	1	1	0
Hispanic	0	2	0
Area of Deprivation Index state values			
1‐4 (least deprived)	6	14	1
5‐7	6	5	2
8‐10 (most deprived)	14	4	2

a One participant is excluded in Area Deprivation Index due to being suppressed in the calculation. Values reflect interim enrollment.

**Table 4. T4:** Current study participant enrollment (May 31, 2026).

Enrollment	Sickle cell disease (aim 1)	Typically developing (aim 1)	Sickle cell disease (aim 2)
9 months	12	10	5
18 months	22	15	0
30 months	18	16	0
Total unique participants	26	24	5
Total approach	84	44	13
Total consent	35	37	7

Participants in aim 1 for the SCD cohort all identify as Black or African American; 7 participants in the comparison cohort identify as Black or African American, 15 identify as White, 1 identifies as Asian, and 1 identifies as more than one race.

Aim 1 enrollment is ongoing; 50 participants are needed to fulfill the recruitment goal of aim 1 (n=100), 24 more in the SCD cohort, and 26 more in the comparison cohort. Enrollment in aim 2 began in July 2025, and 20 more participants will be recruited to this pilot intervention. As of May 31, 2026, one participant has initiated and completed 5 home visits.

## Discussion

### Anticipated Findings

This study will provide the first prospective characterization of developmental trajectories in children with SCD across the first 3 years of life, using a psychometrically robust assessment battery and a demographically matched comparison cohort. Despite evidence that developmental delays affect at least 50% of young children with SCD [6,26], the trajectory of these delays from infancy has not been rigorously evaluated, and no disease-specific intervention has been formally tested in this age group. The SCCCD intervention combines OT, the PAT curriculum, and SCD-specific caregiver education and is adapted from a pilot protocol with demonstrated feasibility and preliminary effectiveness in this population [20,26]. The findings from this study will establish preliminary evidence for the SCCCD as a structured, home-based approach to improving developmental outcomes in children with SCD and will generate the implementation science evidence needed to support broader scale-up.

### Protocol Adaptations

Two protocol adaptations were made following IRB approval and are documented here in the interest of transparency. First, in response to caregiver feedback regarding barriers to on-site attendance, evaluations may now be conducted in the family’s home for participants residing within the Greater St. Louis Metro area. This adaptation reflects the access barriers that have historically limited participation of Black and African American families in research and clinical programs and is consistent with the home-based delivery model of the SCCCD intervention. Second, the SWYC [43] was added to the assessment battery following input from community advisory board members, who recommended its inclusion to capture additional environmental and contextual factors and to allow comparison with other commonly used developmental screening measures used in community settings.

### Limitations

Several limitations should be acknowledged. Recruitment is concentrated at a single site, which may limit the generalizability of the findings to SCD programs in other regions. The English-language-only inclusion criterion, necessary given the validation constraints of the assessment measures, excludes non-English-speaking families and limits the diversity of the sample. Aim 2 does not include a randomized comparison condition; developmental outcomes for children who receive the SCCCD intervention will be compared to the aim 1 observational cohort, which introduces the potential for selection bias. Some outcome measures rely on caregiver report, which may be subject to response bias. Finally, participants who do not complete all evaluation time points will be analyzed using available data, and attrition will be documented and reported.

### Conclusions

Early identification of developmental delays in children with SCD remains inconsistent, and the window for intervention in the first 3 years of life is frequently missed [12,15]. This study directly addresses that gap by characterizing developmental trajectories from infancy, testing a home-based intervention designed for this population, and identifying the contextual factors that will inform future implementation. The results will be shared through community partners, peer-reviewed publications, and scientific meetings. The study design reflects a deliberate commitment to reducing structural barriers to participation for families, including home-based delivery, flexible scheduling, transportation support, and ongoing community advisory board engagement. The results will provide the foundation for a future randomized controlled trial of the SCCCD intervention and inform clinical recommendations for developmental screening and early intervention in SCD.
